### Objectives

The overall aim of this survey is to estimate the frequency of various interventions applied to newborn infants in the DR and to investigate the impact of possible influencing factors such as centre size and location, level of neonatal care, working hours and weekly periods.

The main objectives of this study are:
1.To estimate the total frequency of interventions given to neonates in the DR in order to support neonatal transition and to compare this estimate with prior data.2.To estimate the frequency of single supportive interventions applied to neonates in the DR.3.To investigate the impact of the following patient-specific factors on supportive interventions:
a.gestational age (separated into different gestational age groups)b.mode of birth (c-section vs. vaginal delivery)4.To investigate the impact of the following structural factors on frequency of single interventions:
a.Designated level of neonatal care according to the definition of the American Academy of Pediatrics (AAP) (15)b.Centre size (defined by total number of newborn infants in 2021)c.Presence of trained neonatologists 24/7d.Centre location (defined by country)5.To investigate the impact of the following organisational factors on frequency of supportive interventions:
a.Weekly period of birth (Monday–Friday vs. weekend)b.Daily period of birth (00.00–08.00, 08.00–16.00, 16.00–00.00)Further objectives include:
6.To further elucidate the mode of respiratory support by analysing the combined frequency of the use of CPAP, non-invasive ventilation and invasive ventilation, and by analysing the frequency of primary intubation (without application of non-invasive respiratory support).7.To generate current data regarding surfactant administration in the DR by comparing the frequency of less-invasive surfactant administration versus application *via* endotracheal tube.8.To investigate the frequency of laryngeal mask use as an alternative airway management tool in the DR.9.To further elucidate the current practice regarding the route of drug administration by comparing the frequency of peripheral venous, umbilical venous and intra-osseous access in the DR.10.To evaluate certain indicators of adherence to ERC guidelines (e.g., oxygen supplementation in resuscitation of early pre-term infants).

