### Sample size

The targeted sample size was decided upon empirically. The rarest described intervention in the literature is the administration of epinephrine with a frequency of as low as 0.05% and we wanted to collect data on at least 20 infants receiving this intervention. Therefore, the calculated total number of births during the study period must equal or exceed 40,000. We expect at least 500 births per participating hospital during the study period, leading to a target of 80 participating hospitals. Assuming an intervention rate of 10%, this results in a sample size of 4,000 infants receiving interventions. As we wish to be able to strive to have meaningful comparisons between different levels of neonatal care and different healthcare systems, we are looking to include hospitals from 20 countries and if possible multiple hospitals of different neonatal care levels per country. Ideally, this would mean 4 hospitals per country, one per level of neonatal care. Participating hospitals will be recruited *via* direct contact, referrals by other hospitals and presentation of the study protocol at scientific congresses.

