### Study variables

For every included neonate the following data are collected:
•Weekly period of birth (Mo–Fr/Weekend)•Time period of birth (8:00–16:00/16:00–0:00/0:00–8:00)•Completed week of gestation•Mode of birth (c-section/no c-section)•Application of the following items during neonatal resuscitation:
○Respiratory support:
◾ Initial inflations◾ CPAP◾ Non-invasive ventilation◾ Oxygen supplementation○Airway management:
◾ Suction*◾ Laryngeal mask◾ Endotracheal intubation + invasive ventilation○Drug application:
◾ Surfactant administration (*via* endotracheal tube)◾ Less-invasive Surfactant administration (LISA)◾ adrenaline◾ Caffeine○Vascular access
◾ Peripheral IV access*◾ Umbilical venous access◾ Intraosseous access○Chest compressions (if performed at least once)Marked items (*) will only be recorded if performed together with other interventions due to practicability aspects. Tactile stimulation is not recorded because while it is most likely applied to every neonate, the management varies widely between centres and there exists no consensus on the most effective stimulation method (16).

For detailed definitions of the variables see Table 1.

**Table 1 T1:** Definitions of study variables/data collection form items.

Study variable	Definition
Initial inflations	Positive pressure application using a facemask (at least ≥10 cm H_2_O over PEEP) over at least 2 s at least once before any other respiratory support
CPAP	Continuous positive pressure application (≥5 cm H_2_O) with sufficient device positioning and regardless of interface and pressure driver
Non-invasive ventilation	Intermittent positive pressure ventilation (iPPV) at least two times in a row regardless of interface and pressure driver; initial inflations excluded
Suction	Use of any suction device for airway clearance
Laryngeal mask	Insertion of laryngeal mask as airway device
Oxygen supplementation	Application of any additional oxygen, FiO_2_ > 0.21
Intubation + invasive ventilation	Ventilation *via* endotracheal tube (ETT); not to be ticked if intubation was used as mean for surfactant administration and the infant was extubated prior to the end of neonatal resuscitation
Surfactant *via* ETT	Surfactant administration *via* endotracheal tube, regardless of continuation of invasive ventilation after Surfactant administration
Less-invasive surfactant administration	Any other form of Surfactant administration less invasive than *via* endotracheal tube

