### Data analysis

Data will be analysed globally and for specific, predefined subgroups for every independent variable (e.g., completed week of gestational age, mode of birth, designated level of neonatal care).

Descriptive analysis will be performed on all study variables including absolute numbers and percentages as well as median and range for numerical variables. For all observed interventions confidence intervals will be calculated on a confidence level of 0.95. Additionally, statistical analysis regarding possible correlations will be performed on all study variables using phi coefficient and chi square test of independence. Statistical analyses and graphical presentations will be performed using R (The R Foundation for Statistical Computing, Vienna, Austria).

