## Anticipated results

We are expecting that the targeted sample size of at least 4,000 neonates receiving interventions will be collected within 1 year of enrolling the first hospital. To reduce bias, we are looking to collect data on equal amounts of births for every level of neonatal care and to include a hospital of every level of neonatal care from every participating country.

The minimum of anticipated results of descriptive and statistical analysis is listed in Table 2. Further results of additional analysis might be added if the need emerges during the data analysis process. Selected results of descriptive analysis and significant statistical analysis will be presented in graphical form as diagrams. All results regardless of significance will be presented in tabular form, at the least as supplementary material of the planned publication.

**Table 2 T2:** List of anticipated results of descriptive and statistical analysis.

Descriptive analysis	Statistical analysis
Total intervention frequency (global and stratified into subgroups sorted by mode of birth, level of neonatal care, center size, country, weekly period of birth, daily period of birth)	Significant differences in total intervention frequency between the stratified subgroups (mode of birth, level of neonatal care, center size, country, weekly period of birth, daily period of birth)
Frequency of single supportive interventions (global and stratified into subgroups sorted by gestational age, mode of birth, level of neonatal care, center size, country, weekly period of birth, daily period of birth)	Significant differences in single supportive intervention frequency between the stratified subgroups (mode of birth, level of neonatal care, center size, country, weekly period of birth, daily period of birth)
Combined frequency of CPAP, non-invasive ventilation and invasive ventilation and frequency of primary intubation (without application of non-invasive respiratory support)	Significant differences in single supportive intervention frequency for neonates receiving interventions stratified by gestational age groups

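### Level of care, centre size and gestational age are tested only with methods that ignore their order; add a trend or continuous term beside the chi-square

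*Protocol article*

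**What the plan says.** The Data analysis section of the protocol article names two association methods for every variable: "statistical analysis regarding possible correlations will be performed on all study variables using phi coefficient and chi square test of independence". The abstract names the same two. No trend test, ordinal method or regression appears in the article.

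Three of the factors are ordered or numeric:

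- **Gestational age.** Study variables records it as "Completed week of gestation". Objective 3a uses it as "gestational age (separated into different gestational age groups"). Table 2 plans to report "Significant differences in single supportive intervention frequency for neonates receiving interventions stratified by gestational age groups".
- **Centre size.** Objective 4b takes it from each site's number of newborns in 2021, which is a count. Table 2 handles it as a stratified subgroup.
- **Level of care.** The American Academy of Pediatrics levels are ordered, and the Sample size section implies four: "Ideally, this would mean 4 hospitals per country, one per level of neonatal care".

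The article gives no number of groups or cut-points for gestational age or centre size, and no alpha for the tests.

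**The concern.** A chi-square test of independence treats ordered groups as unordered names. It spreads its power over every possible pattern of differences, so it is less sensitive to a steady rise or fall than a test aimed at one. With a yes/no intervention across several groups, phi is the square root of chi-square divided by N. It has no sign, and says nothing about change per week, per level or per doubling of births. Grouping also discards the differences within groups and makes the result depend on where the cuts fall.

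Objectives 3a, 4a and 4b ask about the impact of these three factors, and a gradient is a natural form for that impact. The loss matters most where events are few. Adrenaline is the clearest case, because the survey was sized on about 20 such infants.

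**Working it through.** **1. The plan's own size.** From the Sample size section: 20 / 0.0005 = 40,000 births; 40,000 / 500 = 80 hospitals; 40,000 x 0.10 = 4,000 infants receiving interventions. These reproduce exactly. The Anticipated results section says "we are looking to collect data on equal amounts of births for every level of neonatal care", so four levels give about 10,000 births each.

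**2. Cost of ignoring order, in general.** Assume two-sided alpha 0.05 (not stated in the article) and an exactly linear gradient. Both tests then have the same non-centrality. A 1-df test has 80% power at non-centrality 7.849. At that value:

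| Groups | df | Critical value | Chi-square power | Loss |
|---|---|---|---|---|
| 3 | 2 | 5.991 | 70.9% | 9.1 points |
| 4 (level of care) | 3 | 7.815 | 64.5% | 15.5 points |

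For four groups the loss is at most 17.0 points, whatever the power of the trend test.

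**3. Adrenaline by level of care.** Inputs: mean rate 0.05%, 4 x 10,000 births taken as independent, and an assumed constant rate ratio between adjacent levels. A ratio of 1.5, for example, gives expected counts of 2.5, 3.7, 5.5 and 8.3, which sum to 20. Simulated power:

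| Rate ratio per level | Chi-square, 3 df | Trend test, 1 df |
|---|---|---|
| 1 (no effect) | 4% | 5% |
| 1.5 | 31–32% | 49–50% |
| 1.7 | 51% | 70% |
| 2 | 74% | 88% |

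**4. Total intervention frequency by level of care.** With mean rate 10% and a step d between adjacent levels, the non-centrality is 10,000 x 5d² / (0.10 x 0.90), again for independent births:

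| Step d | Non-centrality | Chi-square, 3 df | Trend test, 1 df |
|---|---|---|---|
| 0.3 points | 5.0 | 44% | 61% |
| 0.4 points | 8.9 | 71% | 85% |
| 0.5 points | 13.9 | 89% | 96% |
| 1.0 point | 55.6 | about 100% | about 100% |

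**5. What the pooled test does for hospital-level factors.** Level of care and centre size are constant within a hospital. Assume a between-hospital SD of 2 to 4 percentage points around 10%. Then ICC = SD² / 0.09 = 0.0044 to 0.0178, and the design effect 1 + 499 x ICC is 3.2 to 9.9. With no true gradient, the unadjusted test rejects with probability P(chi-square > critical value / design effect): 27–53% with two groups, 39–74% with three and 49–85% with four. An unadjusted trend test is not safe either: at ICC 0.01 (design effect 5.99) it rejects 42% of the time, against 73% for the 3-df chi-square.

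**6. A non-monotone pattern.** With rates of 10.5, 9.5, 9.5 and 10.5%, the non-centrality is 10,000 x 4 x 0.005² / 0.09 = 11.1. Chi-square has 81% power, and a linear trend test has 5%.

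**The case against.** The survey is descriptive and meant to generate hypotheses. Table 2 asks for "Significant differences in total intervention frequency between the stratified subgroups (mode of birth, level of neonatal care, center size, country" and so on, which is a question about group differences that an omnibus test answers. All results are to be tabulated regardless of significance, so a reader can see the direction across ordered groups. Further analyses are allowed if the need emerges. Hospitals graded by a regional equivalent of the levels are admitted, so equal spacing of level scores is an assumption. A U-shape would be missed by a linear trend alone.

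Much of this stands, and it is why a trend term should be added and should not replace the chi-square. It does not remove the point. The article states its method for all study variables, so this is a choice made and not a detail left to a fuller document. An open option to add analyses later is not a plan for them. A table shows direction but gives no estimate per unit.

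Two stronger readings are tempting. A reader might infer one fixed power loss, such as 10 to 23 points, for all three factors. The documents do not support it: only the four levels of care fix a number of groups, and the loss also depends on the shape and strength of the gradient. A reader might also infer that real centre-size gradients will be missed, with a loss of 19 to 25 points. Those figures belong to an analysis with the hospital as the unit, which the article does not describe. The pooled test as described errs the other way (step 5).

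**Conclusion.** The point holds as a cheap improvement. The only association methods named ignore order in three factors that have it, and give neither direction nor effect per unit. That second shortcoming remains at any sample size.

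The power cost is conditional. For a linear gradient, when a trend test has 80% power, it is about 9 points with three groups and 15.5 with four. For adrenaline by level of care it is about 14 to 19 points, assuming independent births and rate ratios of 1.5 to 2. It is negligible for total intervention frequency once steps are about 1 point per level. For gestational age no specific figure can be given, because the groups are not stated.

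For level of care and centre size, over-rejection from clustering is the larger problem in the test as described. The size of that over-rejection rests on the assumed between-hospital SD. Any trend term for these two factors is useful only if it allows for clustering.

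**What to change.** Keep the chi-square and the subgroup tables. Add to the Data analysis section and to the statistical column of Table 2:

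1. **Level of care:** a 1-df trend term (a Cochran-Armitage-type test or a logistic slope), in a form that accounts for hospital clustering.
2. **Centre size:** log(2021 births) as a continuous term in a logistic or binomial regression that accounts for hospital clustering, reported as an odds ratio per doubling of births.
3. **Gestational age:** completed week as a continuous term, with a spline where counts allow, for single interventions among infants who received any. The restriction is needed because sites report only total and c-section births, so there are no birth denominators by gestational age.

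The cost is a few lines of wording and R code, with no new data, sites or infants. The downside is small: a linear trend is weak against non-monotone patterns, and the retained chi-square and the spline cover that.

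### The infant-level chi-square test fixed for all study variables ignores hospital clustering, so the hospital-level comparisons of objective 4 over-reject by an amount that depends on an unstated intracluster correlation

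*Protocol article*

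**What the plan says.** The Data analysis section names one inferential method: "statistical analysis regarding possible correlations will be performed on all study variables using phi coefficient and chi square test of independence". The Abstract names the same two tools. On precision it says: "For all observed interventions confidence intervals will be calculated on a confidence level of 0.95". It does not name the interval formula.

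Objective 4 is "To investigate the impact of the following structural factors on frequency of single interventions", and the factors listed are designated care level, centre size, round-the-clock presence of a trained neonatologist, and country. Care level, annual births and neonatologist availability are recorded once per survey site, and country is fixed by the site. Table 2 plans significance comparisons by care level, centre size and country, for total intervention frequency and for single interventions.

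On numbers, the Sample size section says "the calculated total number of births during the study period must equal or exceed 40,000" and "We expect at least 500 births per participating hospital during the study period", "leading to a target of 80 participating hospitals". On their distribution it says: "Ideally, this would mean 4 hospitals per country, one per level of neonatal care".

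The Data collection and management section gives each site an ID in the central database. The article nowhere mentions clustering by hospital, a design effect, a robust variance or a multilevel model, and its list of limitations does not include clustering.

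**The concern.** The chi-square test of independence assumes that infants are independent. Infants born in one hospital share staff, equipment and local habits, and the Discussion itself expects differences arising from local guidelines and practices. Outcomes within a hospital are therefore likely to be correlated.

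For a factor that is constant within a hospital, this correlation does not cancel. All the information about the factor lies between hospitals, while the test counts infants. Ordinary differences between hospitals can then appear as significant effects of care level, size or country. The article plans to display significant results graphically and to inform future guidelines, so such findings would carry weight. A pooled interval that ignores clustering would also be narrower than its 95% label implies.

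**Working it through.** **The plan's own figures.** 20 infants / 0.0005 = 40,000 births; 40,000 / 500 = 80 hospitals; 40,000 × 0.10 = 4,000 infants receiving interventions. All three reproduce.

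**Inputs from the article.** 80 hospitals; m = 500 births per hospital; 4,000 / 80 = 50 treated infants per hospital; 10% rate; 80 / 4 = 20 hospitals per level; 80 / 20 = 4 per country; 95% confidence.

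**Assumptions.** The ICC is not given; the range 0.001 to 0.05 is used. Tests are two-sided at 5%, and hospitals are of equal size (unequal sizes would raise the design effect).

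**Formulas.**
- Design effect DE = 1 + (m − 1) × ICC.
- Effective N = N / DE.
- Rejection rate with no true effect = P(χ² on df degrees of freedom > 5% critical value / DE).
- Coverage of a simple binomial 95% interval = 2Φ(1.96/√DE) − 1.

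Example: m = 500 and ICC 0.01 give DE = 1 + 499 × 0.01 = 5.99. For four levels (3 df) the critical value is 7.815, and P(χ² > 7.815/5.99) is about 0.73.

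| Infants counted | ICC | DE | Effective N | Two groups | Four levels | 20 countries | Coverage |
|---|---|---|---|---|---|---|---|
| All births, m = 500 | 0.001 | 1.50 | 26,684 | 11% | 16% | 39% | 89% |
| | 0.01 | 5.99 | 6,678 | 42% | 73% | >99% | 58% |
| | 0.05 | 25.95 | 1,541 | 70% | 96% | >99% | 30% |
| Treated, m = 50 | 0.01 | 1.49 | 2,685 | 11% | 15.5% | 38% | 89% |
| | 0.05 | 3.45 | 1,159 | 29% | 52% | 98% | 71% |

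**Interval width.** For a 10% rate over all births the simple half-width is 1.96 × √(0.1 × 0.9 / 40,000) = 0.29 percentage points. This figure is computed here; the article states none. Multiplied by √DE it becomes 0.36, 0.72 and 1.50 points at ICC 0.001, 0.01 and 0.05.

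**Check by simulation.** 2,000 beta-binomial surveys per scenario (80 equal hospitals, no factor effect, m = 500, 10% rate, ICC 0.001 / 0.01 / 0.05) gave:
- four levels: 17%, 73%, 96%;
- two groups: 11%, 43%, 69%;
- 20 countries: 38%, then 100% at both higher ICCs;
- coverage: 89%, 59%, 32%.

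**Factors that vary within hospitals.** In the same simulations a weekend factor with the same split in every hospital rejected in 3% to 6% of surveys in every scenario, so there is no inflation. The same reasoning covers daily period, and mode of birth if the caesarean share is similar across hospitals. If that share varies (assumed mean 30%, SD about 0.145), the rejection rate for mode of birth is 10% at ICC 0.01 and 29% at ICC 0.05.

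**Is the ICC range plausible?** The Discussion cites 4% to 12% for non-invasive ventilation. If hospital rates were spread evenly over that range, ICC = (0.08²/12) / (0.08 × 0.92) = 0.007. If they were split between the two ends, ICC = 0.04² / (0.08 × 0.92) = 0.022. This is indicative only, because the range comes from different studies.

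**The case against.** The strongest reply has four parts.

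1. **The ICC is unknown.** A reader might infer that intervals are bound to be far too narrow and that each structural test is nearly certain to give a false positive. The article does not support that. At ICC 0.001 the four-level test rejects in about 16% of surveys and coverage is about 89%. Two-group factors reach 70% only at ICC 0.05. Care-level tests among treated infants run from about 15% to 52%. Near-certainty for a single test holds only for country from an ICC of about 0.01 (all births) or 0.05 (treated infants), and for care level from about 0.05 with all births. This part stands, and the size must be stated conditionally.

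2. **No interval formula is named.** A simple binomial interval is inferred from the absence of any clustering method, and the formula could sit in a fuller plan. This stands; the point about intervals is conditional. The test is different, because the article names it.

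3. **Not every test is affected.** A reader might extend the criticism to all the chi-square tests. Weekly and daily period, and mode of birth under the condition above, do not support that. This stands.

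4. **The survey is descriptive.** The article disclaims causal conclusions, describes hypothesis generation and promises to tabulate all results whatever their significance. That softens the consequence but does not repair the test: a p-value with the wrong reference distribution is no safer for being exploratory.

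The 10% figures also do not carry over to adrenaline. At 0.05%, 500 births give 0.25 expected cases per hospital, and a mixed model on about 20 events would be hard to fit.

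**Conclusion.** The point holds for hospital-level factors. The article fixes a test that assumes independent infants and applies it to four factors whose independent units are about 80 hospitals. At an assumed ICC of 0.001 to 0.05, with 500 births per hospital and a 10% rate, the 5% test rejects with no true effect in about 16% to 96% of surveys for four care levels, 11% to 70% for a two-group factor, and 39% to over 99% for 20 countries. If simple binomial intervals are used, the pooled interval needs to be about 1.2 to 5.1 times as wide (0.36 / 0.29 to 1.50 / 0.29). The direction of the error does not depend on the assumed ICC as long as it is positive; its size does. These results also rest on equal hospital sizes and on reaching the planned hospital numbers.

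**What to change.** Amend the Data analysis section before analysis as follows.

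- For care level, centre size, neonatologist presence and country, replace the infant-level chi-square with a test that accounts for hospital: a Rao-Scott chi-square, GEE clustered on hospital, or logistic regression with a random hospital intercept. Do the same for mode of birth if the caesarean share varies between hospitals.
- Compute pooled confidence intervals with a hospital-clustered variance or a bootstrap that resamples hospitals, and name the method.
- Report the ICC for each main intervention.
- Keep phi and crude percentages as descriptive summaries.
- For very rare interventions such as adrenaline (about 20 expected events), report frequencies with confidence intervals and fit no mixed model.

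The chi-square can remain for weekly and daily period as far as clustering is concerned. Country comparisons may also remain, provided the test reflects about 4 hospitals per country; restricting them to description would be a matter of preference.

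The cost is small: no new data are needed, since the centre ID is already in the database and R is already the planned software. The price is wider intervals, fewer significant structural comparisons and a little more analysis work.

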**Methods:**

Participating hospitals will collect data on all interventions performed during neonatal resuscitation over a period of 6 months. All hospitals providing perinatal care are eligible regardless of size and designated level of neonatal care. Every neonate requiring more interventions than basic drying and tactile stimulation during the first 30 min of life will be included. The targeted sample size is at least 4,000 neonates who receive interventions. After anonymization, the data is pooled in a common database and descriptive and statistical analysis is performed globally and in subgroups. Possible correlations will be investigated with phi coefficient and chi square testing.

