Peripheral i.v. access	Placement of peripheral IV access regardless of administration of fluids/drugs
Umbilical venous access	Placement of umbilical venous access regardless of administration of fluids/drugs
Intraosseous access	Placement of intraosseous access regardless of administration of fluids/drugs
Chest compressions	Administration of chest compressions at least for one cycle (three compressions) according to ERC guidelines
Adrenaline	Administration of adrenaline at least once, regardless of administration route

Additionally, the following baseline characteristics are collected for every survey site:
•Designated level of neonatal care according to the definition of the AAP (15)•Total births per year (historical data from 2021)•Number of admissions to the neonatal intensive care unit (either in-house or nearest available) per year (historical data from 2021)•Total number of infants born per month during the survey period•Total number of infants born per month *via* c-section during the survey period•Permanent availability of a trained neonatologist either in-house or on call

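### Mode of birth (objective 3b) is tested on a table pooled over about 80 hospitals; if c-section share and intervention rate are correlated across hospitals, the result mixes hospital differences with the mode contrast, and the data to prevent this are already collected

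*Protocol article*

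**What the plan says.** - **Objective.** Objective 3 is one of the main objectives: "To investigate the impact of the following patient-specific factors on supportive interventions". Item b is "mode of birth (c-section vs. vaginal delivery").
- **Pooling.** According to the Abstract (Methods), "the data is pooled in a common database and descriptive and statistical analysis is performed globally and in subgroups". Data analysis adds: "Data will be analysed globally and for specific, predefined subgroups for every independent variable". Hospital is not among the examples given there, nor among the subgroups in Table 2.
- **Test.** The only inferential method named is in Data analysis: "statistical analysis regarding possible correlations will be performed on all study variables using phi coefficient and chi square test of independence".
- **Output.** Table 2 (Anticipated results) lists "Significant differences in total intervention frequency between the stratified subgroups (mode of birth", among other factors), and the same for single interventions.
- **Size.** "We expect at least 500 births per participating hospital during the study period, leading to a target of 80 participating hospitals". The Sample size section seeks 20 countries, ideally with one hospital per care level in each.
- **Data available.** Mode of birth is recorded for each included neonate. Each site reports its monthly births and its monthly births by "c-section during the survey period" (Study variables). The central database holds a pseudonymous centre ID (Data collection and management).

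**The concern.** Mode of birth varies inside every hospital that offers c-section, so each such hospital supplies its own comparison of c-section with vaginal births. A single pooled 2×2 table adds a second, unwanted component: hospitals that perform more c-sections contribute more to the c-section row, and bring their own treatment rate with them.

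The survey deliberately mixes care levels and health systems, and objective 4 asks whether intervention frequency differs by level, size and country. If treatment rate and c-section share go together across sites, the pooled table shows an association that need not exist in any hospital. If they run in opposite directions, it weakens a real one. The answer to a main objective would then depend partly on which hospitals volunteer.

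**Working it through.** **The plan's own figures.** 20 / 0.0005 = 40,000 births; 40,000 / 500 = 80 hospitals (also 20 countries × 4); 40,000 × 0.10 = 4,000 treated infants. All reproduce and are not in dispute.

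**Mechanism.** Take hospitals of equal size with c-section share c and intervention rate r, and let mode have no effect inside any hospital. Write c̄ for the mean share and Cov(c, r) for the covariance across hospitals. The pooled risk difference is then

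Cov(c, r) / [c̄(1 − c̄)].

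It is zero only if share and rate are uncorrelated.

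**Example 1, two hospital types (illustrative).** 20,000 births each; 20% c-section with 6% treated, and 40% with 14%.
- C-section: 4,000 × 0.06 + 8,000 × 0.14 = 1,360 of 12,000 = 11.33%.
- Vaginal: 16,000 × 0.06 + 12,000 × 0.14 = 2,640 of 28,000 = 9.43%.
- RR = 11.33 / 9.43 = 1.20. z = 0.01905 / √[0.10 × 0.90 × (1/12,000 + 1/28,000)] = 0.01905 / 0.00327 = 5.8.
- The formula agrees: (0.10 × 0.04) / (0.30 × 0.70) = 0.01905.

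**Example 2, four levels (illustrative).** 10,000 births per level; shares 20/25/30/40%, rates 5/8/12/15%.
- C-section: 1,260 / 11,500 = 10.96%. Vaginal: 2,740 / 28,500 = 9.61%.
- Pooled OR 1.16, chi-square 16.4 (p < 0.001), with OR 1.00 within every level.

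Both examples use share and rate that rise together almost perfectly. They show that the bias can occur, not how likely it is.

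**Simulation.** 80 hospitals × 500 births, no within-hospital effect, two-sided 5% (the article states no alpha). Inputs not in the documents, and so assumed: the spread of c-section share, the spread of intervention rate between hospitals, and their correlation. The 5–15% rows borrow the overall range in the Abstract as a between-hospital range. Entries are rejection rates of the pooled chi-square.

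| C-section share | Intervention rate | Corr. 0 | 0.3 | 0.5 | 0.8 | −0.5 |
|---|---|---|---|---|---|---|
| 20–40% | 8–12% | 4% | 6% | 8% | 12% | 8% |
| 20–40% | 5–15% | 6% | 12% | 22% | 46% | 21% |
| 15–50% | 8–12% | 5.5% | 8% | 12% | 26% | 12% |
| 15–50% | 5–15% | 6.5% | 24% | 53% | 88% | 51% |

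In these rows the median pooled OR runs from 0.93 to 1.12. The hospital-stratified Cochran-Mantel-Haenszel test rejects in 4.1–5.2%, with a Mantel-Haenszel OR of 1.00.

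A second set lets both quantities vary normally on the log-odds scale around 30% and 10%:
- Wide (SD 0.4–0.5; share about 14–53% and rate about 4–23% at the upper SD): 8–11% at correlation 0, 27–51% at ±0.3, 56–84% at 0.5. Median pooled RR is 1.04–1.11 for positive correlation and 0.94–0.96 for −0.3.
- Narrow: about 5–7% at correlations of 0.3–0.5.
- The stratified test stays at about 4–5% with RR 1.00.

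**With a true effect.** For a within-hospital OR of 1.30 (share 15–50%, rate 5–15%), the pooled OR is 1.21, 1.30, 1.39 and 1.45 at correlations −0.5, 0, 0.5 and 0.8; the stratified OR is 1.30 throughout. The distortion acts as a multiplier (1.30 × 0.93 = 1.21). A true RR of 1.05 with a factor of 0.94 would show as 1.05 × 0.94 = 0.99.

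**The case against.** **Strongest case against.** The bias needs a correlation that the documents do not give. At zero correlation it is essentially absent, and with narrow spreads it is small. High rejection rates partly reflect 40,000 births making a small distortion significant. The survey is descriptive and hypothesis-generating, and the Discussion warns against causal reading. Table 2 is a stated minimum, further analyses are allowed, and an analysis plan that is not shown might stratify. Stratifying by hospital also leaves gestational age and indication uncontrolled.

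**What stands.** The dependence on correlation and spread stands in full and sets the size of the point. Three stronger readings that a reader might infer are not supported:
- That hospital differences are bound to appear as a c-section effect. Neither the sign nor the size of the correlation can be taken from the documents.
- That the result could readily be reversed. With a distortion of 1–11%, that needs a true effect already close to 1.
- That the site-level data are thrown away. The article plans feedback and benchmarking for each hospital, and does not say whether mode is also tested within levels or countries.

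**What does not remove the point.** The Discussion's caution names confounders that are not recorded, whereas hospital is recorded. Analyses added if the need emerges commit to nothing. The point is not a missing detail: the article names a method for a main objective, and that method fits it less well than one the collected data already support. Subgroups by level or country would remove only part of the between-hospital component.

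**Conclusion.** The point holds in conditional form. The only test named for objective 3b ignores hospital, so its error rate and estimate depend on how c-section share and intervention rate happen to be related among participating sites. Under the stated assumptions the false-positive rate lies at about 5–11% with no correlation, 5–51% at ±0.3 and 7–84% at 0.5, the low ends belonging to narrow spreads and the high ends to wide ones. The pooled RR is off by about 1–11%. A large mode effect would survive this; a weak one could be inflated or masked. Since the correlation cannot be known in advance and stratification protects in every scenario examined, the change should be made. The pooled percentages remain a valid description of the surveyed births.

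**What to change.** In Data analysis and Table 2, for mode of birth only, make the inferential analysis a Mantel-Haenszel risk ratio with 95% CI and a Cochran-Mantel-Haenszel test, stratified by hospital. Treated infants by mode are the numerators, and each site's reported total and c-section births supply the denominators. Use the exact conditional version for rare interventions. Present the pooled percentages as description.

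**Cost.** One or two sentences and a few lines of R; no new data. Hospitals with no c-section births, or with no events for an item, contribute nothing to this contrast. For an item as rare as the 20 expected epinephrine cases over 80 sites, most strata will be empty. A single summary ratio may also average over an effect that differs between hospitals. The text should state that stratification removes confounding by hospital only, not by gestational age (for which no site denominators are collected) or by indication.
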